### Primary outcomes

• Health status; measured using the WOMAC Osteoarthritis Index for OA of the knee (WOMAC LK3.0). Also self-administered, the WOMAC assesses pain, stiffness and physical function [13] and can be completed in less than 5 minutes. Two major studies have shown WOMAC pain, stiffness and physical function subscales are valid and the questionnaire is reliable and sensitive enough to detect changes in health status following a variety of interventions [14,15]

• Quality of life; measured using the Short Form 36v1 (SF-36) questionnaire. This 36 item questionnaire is self administered, and can be completed in about 15 minutes [16]. Scores for 8 sub components reflecting both physical and mental status can be generated. Reliability and validity have been established in numerous studies [16,17].

### Secondary outcomes

• Active range of motion of the knee joints; measured using a long armed Goniometer [18]. The reliability and validity of the goniometer to measure range of motion has been widely documented for knee flexion and extension [18,19].

• Strength of the hamstrings and quadriceps muscles will be measured using a Mecmesin Force Gauge Dynamometer. The dynamometer will be fixed via an adjustable arm to a portable steel frame and stool. Subjects will sit on the stool with hips and knees flexed to 90 degrees. Isometric strength in flexion and extension will be measured in this position. Each knee will be measured 3 times. The first measurement will be a practice and will be excluded from analysis. The two subsequent measures will be averaged for analysis.

• Pain will be assessed at weekly intervals from baseline to the 8-week follow-up assessment. (See Figure 1: Study Design Flow Chart). A 10 cm Visual Analog Scale (VAS) anchored at the left with "no pain" and at the right "worst pain imaginable" will be used for this assessment. The VAS is well established in clinical practice and research for measuring pain levels in arthritis populations [20].

**Figure 1 F1:**
[figure not shown]
Study Design Flow Chart.

• Functional mobility, using a Functional Knee Assessment Test (FKAT) will be assessed using a modification of the "Timed Up and Go" test (TUG). TUG is widely used to assess basic functional mobility in the elderly [21-23]. The test measures the time taken to stand from a chair and walk 6 m, turn around, return to the chair and sit down. For this study the addition of ascending and descending a 15 cm step will be added to the outward walk.

### Statistical Power Calculation

A priori power calculations for this study will be based on the quality of life outcome as measured by the SF-36. Sample size was calculated according to guidelines in the SF-36 Users Manual to determine differences in changes over time between the intervention and control groups using a repeated measures design allowing an inter temporal correlation between scores of 0.60 [16]. The pilot study SF-36 data showed an average improvement of 10 points across the eight domains measured. Assuming this level of improvement is achieved in the intervention group and there is no change in the control group and allowing for a 10% drop out rate, the number of participants required per group will be 60 [16]. In the pilot study, there was a drop out rate of 5% over 3 years, so allowing 10% is a conservative estimate. Differences in changes in functional ability measured using the WOMAC, similar in magnitude to those previously documented [24] would also be detectable in a sample of this size.

### Data Analysis

Data will be analyzed in a blinded manner. Treatment groups will be examined for comparability at baseline. Main comparisons between treatment groups will be performed using an intention to treat analysis. To test the effects of treatment, between group differences in changes over time will be examined using repeated measures ANOVA. Separate analysis will be conducted for each outcome variable. Statistical significance will be inferred at a 2-tailed p < 0.05. Results will not be adjusted for multiple comparisons as all outcomes of interest have been nominated a priori and such adjustment would likely render all findings of interest, despite their clinical importance, non-significant.

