**Methods:**

The effects of standard medical management will be compared with the effects of the OAK program in a single-blind randomized study.

*Participants: *146 male and female participants with established OA knee will be recruited. Volunteers with coexistent inflammatory joint disease or serious co-morbidities will be excluded.

*Interventions: *Participants will be randomized into either intervention or control groups (delayed start). The intervention group will complete the OA knee program and both groups will be followed for 6 months.

*Measurements: *Assessments will be at baseline, 8 weeks and 6 months. SF-36, WOMAC and VAS pain questionnaires will be completed. Isometric quadriceps and hamstring strength will be measured using a dynamometer; knee range of movement using a goniometer; and physical function will be determined by a modified timed up and go test. Data will be analysed using repeated measures ANOVA.

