### Hypothesis

People with osteoarthritis of the knee who complete the OAK Program will report improved quality of life, improved knee function and decreased pain compared with those managed conventionally.

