### Assessments and Procedures

Assessments will be performed by 2 physiotherapists blinded to group allocation; conducted one week prior to the first self-management session (baseline) and on the week following the sixth and final session (week 8). The physiotherapists performing assessments will have no contact with the participants other than during the assessment sessions and will not participate in facilitation of the program. Participants will be assessed by the same physiotherapist whenever possible to ensure consistency.

Members of the control group will also attend assessments at baseline, and week 8. All volunteers will be assessed again 6 months after randomisation. In keeping with intention to treat principles, all participants will be encouraged to attend for follow-up measurements regardless of level of attendance at the self-management intervention. Self reported questionnaires (WOMAC, SF-36, VAS pain) would be mailed out to participants that are unable to attend assessment visits. Program and assessment attendance (at all time-points) will also be collected and collated.

Demographic information will include age, sex, co-morbidities and socioeconomic information. Socio-economic scales will be compiled using "The Index of Relative Socio-Economic Disadvantage" scales [12]. This index provides a weighted value that includes variables that reflect or measure disadvantage. These variables include: low-income, low educational attainment, high unemployment and low skilled occupations.

The dependent variables for the study are listed below.

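### Repeated measures ANOVA in its classical form omits anyone with a missing visit, so it does not by itself deliver the promised intention-to-treat analysis

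*Protocol article*

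**What the plan says.** All references are to the protocol article.

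- **Data Analysis** commits to analysis by intention to treat ("Main comparisons between treatment groups will be performed using an intention to treat analysis") and then fixes the method: "between group differences in changes over time will be examined using repeated measures ANOVA", separately for each outcome. The Abstract repeats the method: "Data will be analysed using repeated measures ANOVA". Neither place says how a participant with an incomplete set of visits is handled.
- **Statistical Power Calculation** arrives at 60 per group, "allowing for a 10% drop out rate". It calls this conservative because the pilot lost 5% over 3 years.
- **Assessments and Procedures** ties intention to treat to follow-up: "all participants will be encouraged to attend for follow-up measurements regardless of level of attendance at the self-management intervention". WOMAC, SF-36 and VAS forms are posted to those who cannot come.
- **Secondary outcomes** says of the VAS: "Pain will be assessed at weekly intervals from baseline to the 8-week follow-up assessment". Strength, range of motion and FKAT need a visit.
- **Hypothesis** concerns people "who complete the OAK Program will report improved quality of life".
- **Discussion** credits the intention-to-treat design with lowering the bias that drop-outs and non-compliers could bring.

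**The concern.** Classical repeated measures ANOVA needs a complete row for each person. Someone with a baseline and an 8-week score but no 6-month score is removed altogether, valid 8-week score included. If the method is run as named and nothing more is done, the analysed set is those seen at every visit, which is not everyone randomised.

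Participants know their allocation, and controls are waiting for a delayed start. Loss may therefore differ between arms and depend on how people are doing. Removing incomplete cases could then let in the drop-out bias that the Discussion says the design guards against. It would also discard scores already collected.

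Two smaller matters sit beside this. The classical F test assumes sphericity, which a run of weekly pain scores may not satisfy. And the Hypothesis is worded for programme completers, whereas the analysis is to be by allocation.

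**Working it through.** **1. The plan's own figure.** 60 per group with 10% loss leaves 60 × 0.90 = 54 per group, 108 in all. The article gives neither SD nor power, so 60 can only be back-solved. With a 10-point difference, correlation 0.60 and two-sided 5%:

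- SD of change = 10 × √(54/2) / (1.960 + 0.842) = 18.5 at 80% power. Raw SD = 18.5 / √(2 × (1 − 0.60)) = 20.7.
- At 90% power the same steps give 16.0 and 17.9.

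An assumed SD of 20 is therefore reasonable for what follows.

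**2. Power.** Recruiting 146 and losing 10% leaves 146 × 0.90 = 131.4, above 108. Complete-case loss at the planned rate does not threaten power.

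**3. Share with complete data.** If each follow-up reading is missing independently with probability m (assumed), the complete share is (1 − m)^k. The three-visit outcomes have k = 2. The weekly VAS has k = 8, reading the schedule as one score a week after baseline.

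| m (assumed) | Three visits | Of 146 | Weekly VAS | Of 146 |
|---|---|---|---|---|
| 2% | 96% | 140 | 85% | 124 |
| 5% | 90% | 132 | 66% | 97 |
| 10% | 81% | 118 | 43% | 63 |

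Independence is the unfavourable case for the VAS. If the planned 10% simply leave and everyone else reports every week, 90% are complete however many weeks there are.

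**4. Possible bias.** Assumptions: SD 20; correlation 0.60 between any two visits; control loses 5% at random before 6 months; OAK loses 35% of those below the median 8-week change and 5% of those above it, 20% overall.

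- SD of change = 20 × √0.8 = 17.9. The two halves have mean 8-week changes 0.798 × 17.9 = 14.3 points below and above the arm mean.
- Excess of better responders among OAK completers = (0.95 − 0.65) / (0.95 + 0.65) = 0.1875.
- Shift in 8-week change among completers = 0.1875 × 14.3 = 2.7 points.
- The 8-week and 6-month changes correlate 0.5 under this structure, so the 6-month shift = 0.5 × 2.7 = 1.3 points.

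A simulation of 4,000 runs with 73 per arm agrees for 6 months. The complete-case difference is 1.3 when the truth is 0 and 11.3 when it is 10. Using all observed scores gives about 0.0 and 9.9.

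That scenario loses 12.5% on average, more than the plan allows for. With 25% and 5% lost in the two OAK halves (15% overall; 10% averaged over the arms), the excess is 0.20/1.70 = 0.118. The shifts are then 0.118 × 14.3 = 1.7 points at 8 weeks and 0.8 at 6 months.

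**5. Sphericity.** Simulating the uncorrected group-by-time F test under the null (9 weekly scores, 54 per arm, assumed first-order serial correlation 0.6, 0.8, 0.9) gives type I error of about 7–8%, 10% and 11%. A Greenhouse–Geisser correction brings it to 4–5%. With three visits and serial correlation 0.6, the uncorrected test gives about 5%.

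**The case against.** A reader might infer that the plan contradicts itself, or that it sets up a completer analysis. The article does not support that. Nowhere does it restrict the analysis to people seen at every visit. Intention to treat in the sense of analysing by allocated arm and following everyone up is compatible with repeated measures ANOVA, for instance after imputation. A rule for missing data is commonly left to a fuller protocol or analysis plan, and its absence here is not the point. What stands is narrower: the article does fix a method, and in its ordinary form that method does not have the property claimed for the design.

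The mailed questionnaires are a real safeguard. They cover both primary outcomes and the VAS, so losses that cannot be mailed fall on secondary outcomes only. The 5% pilot loss also suggests that drop-out may be small.

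The VAS figures could be read as properties of the plan. They are not. They need independent weekly gaps, all weekly scores in one model and an uncorrected test, none of which the article states; the Abstract lists the VAS with outcomes assessed at three visits. Sphericity thus concerns at most one secondary outcome, and a routine correction deals with it.

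The Hypothesis wording does not define the analysis set either. It is an inconsistency of language with Data Analysis and with Assessments and Procedures.

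**Conclusion.** The point holds in a limited form and should be corrected. Repeated measures ANOVA in its classical form does not by itself include everyone randomised, and so does not by itself protect against drop-out bias. The harm is possible bias; power is not at risk (131 against 108).

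Under the assumptions shown, the bias in the 6-month SF-36 difference is about 0.8 to 1.3 points, or 8% to 13% of the 10-point planning effect. At 8 weeks it is about 1.7 to 2.7 points, because valid 8-week scores are discarded. It favours the programme if poorer responders leave the OAK arm, would reverse if better responders left, and vanishes if loss is unrelated to outcome. The SD, the loss pattern, the weekly missingness and the serial correlations are all illustrations and not figures from the article.

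Exposure is lowest for WOMAC and SF-36. It is greatest for strength, range of motion and FKAT, and for the weekly VAS if it is analysed as one series.

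**What to change.** - In Data Analysis and in the Abstract, replace repeated measures ANOVA with a likelihood-based mixed model for repeated measures that uses every observed score, with participants in the arm to which they were allocated. Use an unstructured covariance for the three-visit outcomes and, for the weekly VAS, a covariance structure that does not assume sphericity.
- Because that model relies on data being missing at random, add one sensitivity analysis for data not missing at random.
- In Hypothesis, refer to people allocated to the programme and not to those who complete it.

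Imputation before ANOVA would also be defensible, but the mixed model is simpler to state and keeps the partial data directly. It cannot recover physical tests that were never done, which is a further reason for the sensitivity analysis. The cost is wording and slightly more analysis work, with standard software and no extra data or participants.

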## Abstract

**Background:**

An education self-management program for people with osteoarthritis (OA) of the knee was designed to be delivered by health professionals, incorporating their knowledge and expertise. Improvement in quality of life, health status and pain in response to this program has previously been demonstrated in an uncontrolled pilot study. To more rigorously test the effectiveness of the program we will undertake a randomised controlled trial of people with OA of the knee offering specific self-administered exercises and education, in accordance with the principles of self-management.

Aim: To determine whether an education self management program for subjects with Osteoarthritis (OA) of the knee (OAK program) implemented by health professionals in a primary health care setting can achieve and maintain clinically meaningful improvements compared standard medical management in a control group.

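### The only stated test of treatment effect, read as a group-by-time interaction over three visits, does not match the aim to achieve and maintain improvement: a gain lost by 6 months meets it as readily as a gain kept

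*Protocol article*

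**What the plan says.** The aim in the abstract's Background is to find out whether the program "can achieve and maintain clinically meaningful improvements compared standard medical management in a control group". The abstract's Methods set the visits: "Assessments will be at baseline, 8 weeks and 6 months". According to Assessments and Procedures, the week-8 visit falls in the week after the last of the six sessions, so only the 6-month visit can show whether a gain lasts.

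The Data Analysis section gives the test: "To test the effects of treatment, between group differences in changes over time will be examined using repeated measures ANOVA". Each outcome is analysed separately, and the decision rule is: "Statistical significance will be inferred at a 2-tailed p < 0.05". No primary time point is named, and neither is a contrast at 6 months or between week 8 and 6 months.

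The Statistical Power Calculation section describes one gain ("The pilot study SF-36 data showed an average improvement of 10 points across the eight domains measured"), assumes that "there is no change in the control group", and uses one correlation ("allowing an inter temporal correlation between scores of 0.60"). It does not say at which visit the 10-point difference is expected.

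**The concern.** With two arms and three visits, the group-by-time interaction has 2 degrees of freedom. It rejects when the between-arm difference varies over the visits in any pattern. A gain that appears at week 8 and persists is one such pattern. So are a gain that appears at week 8 and is gone at 6 months, a gain that appears only at 6 months, and a deterioration. The stated criterion treats them alike.

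A benefit seen only in the week after the last session could therefore be significant under the stated rule and be reported as effectiveness, with the maintenance part of the aim untested. The Discussion says the results are meant to guide clinicians and funding bodies, for whom a short-lived and a lasting benefit are different findings.

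**Working it through.** **Inputs from the article.** Three visits; 10-point gain against no change in controls; one correlation, ρ = 0.60; two-sided 0.05; 60 per group after a 10% dropout allowance, so 60 × 0.9 = 54 completers per arm. Planned recruitment is 146, or 73 per arm if 1:1.

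**Assumed.** The article gives neither an SD nor a target power. I use SD = 20.75 and show a range.

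**1. The plan's own figure.** "allowing for a 10% drop out rate, the number of participants required per group will be 60". For a change score, the variance is SD² × 2(1 − 0.60) = 0.8 × 430.56 = 344.45. At 80% power, n = 2 × (1.960 + 0.842)² × 344.45 / 10² ≈ 54, and 54 / 0.9 = 60. So 60 fits an SD of about 20.7 at 80% power, or about 17.9 at 90%. It is plausible, but it cannot be verified from the article.

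**2. Group-by-time test, equal variances and correlations.** The noncentrality is λ = (n/2) × Σ(d_t − d̄)² / [SD²(1 − ρ)], with 2 and 2(2n − 2) = 212 df, where d_t is the between-arm difference at visit t.

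- Kept (0, 10, 10): mean 6.67; squared deviations 44.44 + 11.11 + 11.11 = 66.67.
- Lost (0, 10, 0): mean 3.33; squared deviations 11.11 + 44.44 + 11.11 = 66.67.
- In both cases λ = 27 × 66.67 / (430.56 × 0.40) = 10.45, and power is 82.7%.
- Profiles (0, 0, 10) and (0, −10, −10) also give 66.67, and so the same power.

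The equality does not depend on n, on the SD or on the size of the gain:

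| Completers per arm | SD | Kept | Lost |
|---|---|---|---|
| 54 | 18 | 92.2% | 92.2% |
| 54 | 20.75 | 82.7% | 82.7% |
| 54 | 25 | 66.2% | 66.2% |
| 54 | 30 | 49.8% | 49.8% |
| 73 | 20.7 | 92.9% | 92.9% |

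A 20,000-run simulation (54 per arm, SD 20.7) gave 82.6% and 83.2%, equal within simulation error.

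**3. Decaying correlation.** Take 0.60 between adjacent visits and 0.36 between baseline and 6 months (54 per arm, SD 20.7). The simulated power of the same test is 73.4% for the kept gain and 80.8% for the lost one. The multivariate version gives 71.6% and 90.2%. The equality breaks, but in favour of the lost gain.

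**4. A 6-month contrast (54 per arm, SD 20.75, ρ = 0.60).**

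- As a change score: SE = √(2 × 344.45 / 54) = 3.57; 10 / 3.57 = 2.80; power 79% for the kept gain.
- Baseline-adjusted: variance 430.56 × (1 − 0.36) = 275.56; SE = √(2 × 275.56 / 54) = 3.19; 10 / 3.19 = 3.13; power 87%.
- For the lost gain the true 6-month difference is 0, so either version rejects in the favourable direction 2.5% of the time.

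**5. Both contrasts required.** Given baseline, the two follow-up scores correlate (0.60 − 0.36) / (1 − 0.36) = 0.375. The probability that both baseline-adjusted contrasts are significant and favourable for the kept gain is 79% by the bivariate normal approximation (78% in a 20,000-run simulation that fits the baseline adjustment). For the lost profile, and for the late profile (0, 0, 10), it is at most 2.5%.

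**The case against.** The strongest reply is that a repeated measures ANOVA can supply planned contrasts at each visit, and that a condensed article may leave these to a fuller plan. The first part stands. A reader might infer that the method cannot address maintenance at all; the documents do not support that, because the limitation belongs to the omnibus interaction and not to the model. The second part does not remove the point. The article does not leave the test open: it states one, with a significance rule, and that rule can be met by a result the aim does not allow.

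Secondly, the 2-df interaction is a reading. The article speaks in the plural of differences and comparisons and of a two-tailed p, which would also fit separate changes from baseline to each follow-up visit. That is fair, and the point is conditional on the reading. If separate changes were meant, the article should say so and say which of them decide the conclusion. Weekly VAS pain, collected only to week 8, is a different case.

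Thirdly, maintenance appears only in the abstract's aim; the Methods aim and the Hypothesis speak of improvement. This lowers the weight of the point, but the abstract's aim is explicit.

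Fourthly, the visit means would show the direction and any loss of the gain. They would, but the decisive visit would then be chosen after seeing the data.

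Three further inferences should be resisted:

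- **The power calculation was made for a different test.** This is not shown; its wording parallels that of the analysis section.
- **Naming 6 months raises power from 83% to 87%.** The 87% includes baseline adjustment, which the 83% does not. As a change score the 6-month contrast has 79%.
- **A 6-month contrast alone would settle the aim.** It would also pass a profile with nothing achieved at week 8.

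**Conclusion.** The point holds as a mismatch between the stated criterion and the stated aim. Under equal variances and a common correlation, a gain kept and a gain wholly lost at 6 months have exactly the same chance of a significant interaction. The level of about 83% rests on 54 completers per arm and an assumed SD of 20.75; the equality rests on neither. Where correlation decays with time, the case examined favours the lost gain, so relaxing the assumption in that direction does not rescue the test.

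A significant result therefore does not by itself show benefit at 6 months. This should be corrected before analysis, but it is not a fatal flaw: the visits, the data and the model family already support the right comparison, and only the basis for the conclusion needs to be fixed.

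**What to change.** In the Data Analysis section, for each primary scale, replace the omnibus test as the basis for the conclusion with two pre-specified 1-df between-arm contrasts, each with a 95% CI: week 8 (achieved) and 6 months (maintained). Estimate both from one longitudinal model with visit as a category and adjustment for baseline. Claim that improvement was achieved and maintained only if both contrasts are met in the favourable direction. The interaction test may still be reported as supporting information.

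The cost is wording only, with no added visits, measurements or participants. There are two downsides. A purely short-term effect could be reported only as short-term. And under the assumptions above, power for the joint claim is about 79%, against 83% for the omnibus test.

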### Group allocation

Volunteers will be randomized in blocks to ensure manageable numbers for intervention groups. Pre-prepared cards indicating group assignment will be placed in sealed opaque envelopes and drawn as a lottery by a third party for allocation to treatment groups. In order to ensure optimum group sizes, allocation will not take place until a whole block has been recruited

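### Comparing changes from baseline without adjusting for baseline gives up about 20% in variance at the plan's own correlation of 0.60; the test is valid but less precise than it could be

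*Protocol article*

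**What the plan says.** The Data Analysis section fixes the treatment test: "between group differences in changes over time will be examined using repeated measures ANOVA", by intention to treat, separately for each outcome, at a two-sided 5% level. It names no baseline covariate. Baseline appears there only as a check: "Treatment groups will be examined for comparability at baseline". Assessments are at baseline, 8 weeks and 6 months.

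The Statistical Power Calculation section sizes the trial on the SF-36 for differences in change, using a "repeated measures design allowing an inter temporal correlation between scores of 0.60". The effect comes from the pilot: "The pilot study SF-36 data showed an average improvement of 10 points across the eight domains measured". It is assumed that "there is no change in the control group". The result is stated as "allowing for a 10% drop out rate, the number of participants required per group will be 60". Neither an SD nor a power is given.

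On allocation, the article says: "Volunteers will be randomized in blocks to ensure manageable numbers for intervention groups". The Data Analysis section does not mention block.

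**The concern.** When baseline is one of the repeated outcomes, the group-by-time contrast between baseline and one follow-up is the difference between groups in mean change. A change score subtracts the whole baseline value. When the correlation is below 1, that is more than the baseline predicts of the follow-up score, so noise is added back. Regression on baseline subtracts only the predictable part.

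Two things are at stake:

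- **Precision.** The treatment effect is estimated with a larger variance than the collected data allow.
- **Chance imbalance.** If the groups happen to differ at baseline, regression to the mean moves the change-score estimate in a predictable direction. A group that starts worse tends to show more improvement.

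**Working it through.** **Inputs from the article.** Correlation ρ = 0.60 (SF-36); effect 10 points against no change in controls; 60 per group including 10% dropout; two-sided 0.05; 146 recruited in total.

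**Assumptions not in the article.** Equal SD σ at each time point; a power of 80% or 90%; 1:1 allocation.

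**1. The plan's own figure.** 60 × 0.9 = 54 evaluable per group, and 54 / 0.9 = 60. From n = 2·SD_c²·(z₀.₉₇₅ + z_power)² / δ², the SD of change that makes n = 54 is SD_c = 10·√27 / (z₀.₉₇₅ + z_power), and σ = SD_c / √0.80.

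| Assumed power | SD_c | σ |
|---|---|---|
| 80% | 51.96 / 2.802 = 18.5 | 20.7 |
| 90% | 51.96 / 3.242 = 16.0 | 17.9 |

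With neither SD nor power stated, 60 can only be back-solved. It is neither confirmed nor refuted.

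**2. Variance per participant at one follow-up, in units of σ².**

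- Change score: 2(1 − ρ) = 2 × 0.40 = 0.80
- Baseline-adjusted: 1 − ρ² = 1 − 0.36 = 0.64
- Ratio: (1 + ρ)/2 = 0.80, so 20% lower with adjustment

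This step needs no SD and no power. The detectable difference at fixed n and power shrinks by √0.80 = 0.894, for example from 10 to 8.9 points.

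**3. Sensitivity to ρ.** The reduction is 1 − (1 + ρ)/2.

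| ρ | 0.4 | 0.5 | 0.6 | 0.7 | 0.8 |
|---|---|---|---|---|---|
| Reduction | 30% | 25% | 20% | 15% | 10% |

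**4. Mean of both follow-ups, all correlations 0.60.** Change: (1 + ρ)/2 + 1 − 2ρ = 0.80 + 1 − 1.20 = 0.60. Adjusted: (1 + ρ)/2 − ρ² = 0.80 − 0.36 = 0.44. The reduction is 0.16 / 0.60 = 27%.

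**5. Power for 10 points, under the stated assumptions.**

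| Evaluable per group | Assumed σ | Change score | Baseline-adjusted |
|---|---|---|---|
| 54 | 20.7 | 80% | 88% |
| 54 | 17.9 | 90% | 95% |
| 66 (146/2 × 0.9 = 65.7) | 20.7 | 87% | 93% |

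Under the 80% assumption, adjustment would need about 44 evaluable per group instead of 54.

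**6. Chance imbalance.** Given an observed baseline difference D, the change-score estimate is shifted by (1 − ρ)D = 0.4D in size, in the direction opposite to D. With σ = 20.7 and 54 per group, one standard error of D is 20.7 × √(2/54) ≈ 4.0 points, a shift of about 1.6 points. Two standard errors give about 3.2 points, against a planned effect of 10.

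**The case against.** The strongest reply is that nothing here is wrong. The trial is sized for differences in change and analysed for differences in change. Under randomisation that comparison is valid and unbiased on average. With 146 recruited rather than 120, power may be comfortable already. The 0.60 is given for the SF-36 only, and the 20% describes one follow-up contrast, not the whole group-by-time test over three assessments. All of this stands. It limits the point to efficiency and chance imbalance, but does not remove it, because the gain is positive across the correlations shown and uses data already collected. Nor is the choice merely left open for an unseen analysis plan, since the article names the method.

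A reader might infer more in four ways that the article does not support:

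- **That omitting the randomisation block adds to the 20% or misstates the standard error.** All of the 20% comes from the baseline score; a correlation over time says nothing about block. Stable differences in level between recruitment cohorts cancel in a change score. Where allocation is balanced within blocks, leaving block out generally makes the standard error too large, which is conservative. No block effect is given, and the model terms may be in an analysis plan that is not shown.
- **That 20% of the achievable variance reduction is lost.** The 20% is a share of the change-score variance. Against analysing the follow-up score alone (variance 1σ²), adjustment saves 0.36σ² and the change score saves 0.20σ², so the share forgone is 0.16 / 0.36 = 44%.
- **That 80% power and an SD of about 20.7 are the plan's figures.** They are back-solved assumptions.
- **That baseline tests will decide the analysis.** The article says only that comparability will be examined. It describes neither a significance test nor a decision that depends on one.

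**Conclusion.** The point holds as a worthwhile improvement, not as the correction of an error. At ρ = 0.60 and equal variances, the planned comparison at one follow-up has variance 0.80σ² where 0.64σ² is available. That 20% rests only on the article's SF-36 correlation and the equal-variance assumption; other outcomes may have other correlations and so a larger or smaller gain. The power gains (80% to 88%, 90% to 95%, or 87% to 93% with about 66 evaluable per group) are illustrations that depend on an assumed power and the SD it implies. The exposure to chance imbalance, about 0.4 of the baseline difference, is a separate reason for the same change.

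**What to change.** Revise the treatment-effect sentence in Data Analysis. For each outcome measured at both follow-ups, analyse the 8-week and 6-month scores in a longitudinal model adjusted for that outcome's baseline score, or use a constrained-baseline longitudinal model. State that this is pre-specified and applies whatever the observed baseline comparability.

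A factor for randomisation block may be added, or the text can say where that is settled. No gain from it can be quantified from the article.

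The cost is one sentence of analysis wording. Baseline scores are already collected, and no participant, visit or procedure changes. The sample size can stay as it is.
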